### Trial design {8}

We will conduct a stepped-wedge, randomized clinical trial of a multi-faceted educational and care-process based intervention designed to improve the guideline-concordant care of patients with BPPV in the emergency department. The overall design includes an ED-level implementation and embedded, patient-level dissemination strategies which will allow evaluation of both implementation and effectiveness outcomes. Our study design and proposed methods are aligned with methodological standards in a stepped wedge, randomized clinical trial. The overall study period will be approximately 24 months. The study will start with a 6-month pre-intervention period. This will be followed by staggered intervention at the 15 EDs in 11 waves (some medical centers will be paired based on the medical service area) and then an approximately 6-month post-intervention period. The order that each ED receives the intervention will be randomized. The intervention will be provided as a complete package during the month each hospital is randomized. Concurrently, patients will be recruited before and after the physician level intervention is implemented at each ED. Enrolled participants will complete a survey to obtain baseline information and then randomized individually, stratified by sex, age, and medical center, to the intervention or control arm using central computerized randomization. The intervention arm will be sent intervention materials via patient specified preferred electronic communication. The control arm will be provided with the hospital’s standard post-discharge materials.

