### Sample size {14}

#### ED level

The Kaiser Permanente Southern California study site is comprised of 14 ED facilities, which collectively had nearly 40,000 dizziness visits in 2017. We plan to collect data on these visits for approximately 24 months. Thus, for the ED-level strategy, we will evaluate documentation of the DHT and CRM in >80,000 dizziness visits anticipating an increase in volumes over time. We hypothesize that the proportion of target visits with DHT/CRM documentation will increase from 7% in the pre-intervention period to 17% in the post-intervention period based on the findings in our estimated target population in DIZZTINCT-1. Even small absolute increases in the frequency of use of the DHT/CRM in the target population are considered clinically meaningful because the DHT and CRM are simple from a resource standpoint, not expensive, low risk and highly effective in clinical trials. With a sample of 80,000 visits, our power to detect an increase in DHT/CRM use from 7% in the control visits vs 17% in the intervention visits will be effectively 100% based on a two-sided test for independent proportions considering clustering at 14 sites, an intraclass correlation coefficient (ICC) by provider of 22% for provider-level variability (from DIZZTINCT-1) and a significance level of 5% (Table 1). We will use a mixed effects model to account for secular trends, hospital- and provider-specific features, and the potential relative association of the various components with the outcome. We estimate that 20% of the annual sample is the target population (80,000 × 0.20 = 16,000 visits) based on best available evidence that showed about 20% of dizziness patients in a national sample have BPPV characteristics. Of the 16,000 visits, approximately 8000 will be pre-intervention visits and 8000 post-intervention visits. With these volumes, we expect 560 (8000 × 7%) visits with DHT/CRM documentation in the pre-intervention period and 1360 (8000 × 17%) in the post-intervention period. Thus, we anticipate at least 1900 visits with DHT/CRM documentation. For modeling purposes, we should be able to easily meet and exceed the general rule of having 10 outcomes for each independent variable to avoid over-fitting. The large number of visits and anticipated outcomes will allow us to more closely examine differences at hospitals and provider types, and the relative influence of the various intervention components. We will be able to monitor use of the CME session, website, app, and reminder system and incorporate these variables in the model specific to the provider. The additional power will allow us to examine differences at hospitals and provider types, and the relative influence of the various ED-level implementation strategies.

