## Assignment of interventions: allocation

### Sequence generation {16a}

#### ED level

The overall study period will be approximately 24 months. After the 6-month pre-intervention period, the sites will receive the intervention in 11 waves. The order will be determined by using a random number generator. The intervention start date at each ED is the date the physicians are auto enrolled for the online CME and the printed education materials (i.e., posters, notecards) are distributed on site.

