## Statistical methods

### Statistical methods for primary and secondary outcomes {20a}

The primary outcome is the dizziness handicap inventory (DHI) which is a continuous (0–100) measure of dizziness disability based on a patient’s responses to 25 survey questions. Higher scores indicate more disability. We will use the Ceballo validated Spanish translation for the Spanish speaking individuals. As a sensitivity analysis, we will substitute 2 Lopez questions because we did not think the Ceballo translation was optimal for the following questions: Does bending over increase your problem? (Ceballo: When you get up, does your problem increase?]-Does turning over in bed increase your problem? (When you get out of bed, does your problem increase?] The DHI outcome will be obtained at 1-week intervals after the ED visit for 4 consecutive weeks—corresponding to 4 assessments. We will obtain 4 weekly assessments as we expect that time to recovery will vary given our heterogenous dizziness population. The primary analysis will be a multi-level model as follows: dependent variable (outcome) is the DHI (continuous); fixed independent variables are ED-level intervention group (0/1), patient intervention group (0/1), an interaction term of ED-level intervention with patient intervention group, patient severity at the time of ED visit (continuous), and assessment number (categorical, 1–4); and including a random ED-level intercept. This method allows us to capture variability in recovery over time while maintaining all of the variation in our continuous outcome. We include the severity at the time of the ED visit measure in the model to adjust for baseline disability, protecting against any random imbalances. Because of the two concurrent interventions (ED-level [0/1], patient-level [0/1]), patients will be in either a no intervention group, an ED-level intervention group only, a patient-level intervention group only, or both an ED- and patient-level intervention group. For a secondary analysis, we will add an interaction term of assessment number and intervention group (i.e., a 3-way interaction term of ED-level intervention, patient-level intervention, and assessment number) to further evaluate if any association of intervention group with the DHI outcome is modified by time to assessment. We will make comparisons of the effectiveness of the intervention at each time interval by estimating average marginal effects from our secondary model and comparing marginal effects using Wald Tests. We do not anticipate that our interventions will have differential effects by sex, either at the patient or provider level. Dizziness presentations in the emergency department are more common in females, although at this point there is little biological understanding of the reason for this. For the patient level analyses, we will disaggregate the data and perform analyses separate for male and female patients to assess for heterogeneity. In secondary analyses, we will explore if patient factors (age, sex, Charlson co-morbidities, health literacy) modify the effect of interventions with the outcome. Health literacy will be measured at the first outcome assessment using the BRIEF health literacy tool, 80 which was selected using the Boston University Health Literacy Tool Shed.

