
We initially considered performing the analysis using time to event (Cox proportional hazard model) based on a fixed and pre specified percentage improvement in the DHI from baseline. We felt, however, that this approach had two important limitations. First, there is not an established DHI threshold of success to use for time to event, and the appropriate threshold likely varies by condition. Second, a time to event analysis would dichotomize a continuous variable which substantially comprises statistical efficiency, information, and precision (e.g., true difference in degree of DHI improvement), and power [12, 36, 47, 49].

SPIRIT guidance: Statistical methods for analyzing primary and secondary outcomes. The statistical analysis for secondary and exploratory outcomes will be multi-level regression models as with our primary outcomes. For the cost analysis, the inputs will include tests, medications, procedures, consultations, and level of visit. Additional costs will also be gathered relating to hospital admission and subsequent visits to the ED. Unit costs will be derived from nationally representative sources (e.g., Medicare fee schedule). Costs often have a skewed distribution and thus will be log-transformed to achieve a more normal distribution. The costs in patients treated by pre-intervention providers will be compared to costs in patients treated by post-intervention providers using the t-test and also a generalized linear model (GLM). General concepts for modeling costs will be followed. [40, 46] Reference to where other details of the statistical analysis plan can be found, if not in the protocol.

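### If the ED effect on DHT/CRM is coded as one step from launch, the trend-adjusted estimate reflects mainly the first months; a time-since-launch analysis should be prespecified

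*Protocol article*

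**What the plan says.** All references are to the protocol article.

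- **Trial design {8}.** "The overall study period will be approximately 24 months". "The study will start with a 6-month pre-intervention period", then "staggered intervention at the 15 EDs in 11 waves", then about 6 months after the last wave. Each hospital receives the whole package in its allocated month.
- **Sequence generation {16a}, ED level.** "The intervention start date at each ED is the date the physicians are auto enrolled for the online CME" and printed materials are distributed on site. No transition period is named.
- **Sample size {14}, ED level.** The DHT/CRM effect is framed as a pre/post contrast, 7% against 17%. On the model: "We will use a mixed effects model to account for secular trends, hospital- and provider-specific features". Provider-specific use of the CME, website, app and reminders is also to enter it. The form of the trend and the coding of the ED effect are not given.
- **Statistical methods {20a}.** The only written coding of ED exposure is in the DHI model: "fixed independent variables are ED-level intervention group (0/1), patient intervention group (0/1"), with "assessment number (categorical, 1–4); and including a random ED-level intercept". The time term there is the survey number, not calendar time. For other outcomes: "The statistical analysis for secondary and exploratory outcomes will be multi-level regression models as with our primary outcomes".

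**The concern.** The intervention is education, local champions and reminders. Being enrolled for a CME session is not the same as completing it. The article itself reports low provider participation at non-academic sites in DIZZTINCT-1 and plans to measure training uptake. The first EDs are followed for up to 18 months after launch, so both build-up and fading are possible.

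In a stepped wedge adjusted for calendar time, the later months have few or no unexposed EDs left for comparison. A model with one 0/1 term then takes its information from the months just after each launch and uses long-exposed EDs as controls for newly launched ones. If the effect changes with time since launch, the coefficient is not the average effect over post-launch visits. A programme that works after a learning phase could be reported as weak, and one that fades could be reported as stronger than it was. A larger number of visits narrows the interval around the wrong quantity.

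**Working it through.** **1. What Table 1 assumes.** The text describes a test of two independent proportions. Without clustering, that test gives totals of 330, 1078 and 3800 (370, 1156 and 3960 with continuity correction), not the 468, 2028 and 7800 in Table 1. The stepped-wedge variance for one immediate 0/1 step with categorical periods does give them:

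Var = I s2 (s2 + T t2) / [(I U - W) s2 + (U^2 + I T U - T W - I V) t2]

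The layout that fits is 12 clusters and 13 periods. This is inferred, since the text speaks of 14 or 15 EDs. It gives U = 78, W = V = 650, I U - W = 286, and a last bracket of 2002. Total variance is 0.07 x 0.93 = 0.0651. With ICC 0.22, t2 = 0.01432 and s2 = 0.78 x 0.0651 / m for m visits per cell.

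- 7% vs 17%, m = 3: s2 = 0.01693. Var = 12 x 0.01693 x 0.2031 / (4.84 + 28.67) = 0.00123, SE 0.0351. Power = Phi(0.10/0.0351 - 1.96) = 0.813. Total 3 x 156 = 468.
- 7% vs 12%, m = 13: power 0.824, total 2028.
- 7% vs 9.5%, m = 50: power 0.804, total 7800.

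One visit fewer per cell gives 0.656, 0.794 and 0.796, so each entry is the exact minimum.

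**2. Where a single step puts its weight.** Inputs from Trial design {8}: 15 EDs, 11 waves, 24 months. Assumed: monthly waves in months 7 to 17, four of them pairs, equal ED sizes, linear scale, random ED intercept. 80,000 / (15 x 24) = 222 visits per ED-month. With month effects, the weights by month since launch are 0.32, 0.26, 0.22, 0.16, 0.13, 0.09, 0.06, 0.04, 0.01, then -0.02 to -0.04. Months 1-4 carry 0.32 + 0.26 + 0.22 + 0.16 = 0.96. Months 10-18 carry about -0.29. An ICC of 1.9% or 22% makes almost no difference.

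**3. A 6-month linear build-up by hand** (plateau = 1, effect counted at month end). Estimate = 0.32(1/6) + 0.26(2/6) + 0.22(3/6) + 0.16(4/6) + 0.13(5/6) + (1 - 1.09) = 0.465 - 0.09 = 0.375. True average: each ED loses 5/6 + 4/6 + 3/6 + 2/6 + 1/6 = 2.5 months of effect. With the pairs in the first four waves there are 209 post-launch ED-months, so the average is 1 - 15 x 2.5/209 = 0.82. Ratio 0.46. On a 10-point plateau that is about 3.8 points estimated against 8.2.

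**4. Results with month effects** (estimate / true post-launch average):

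| Assumed curve | Month-end counting | Mid-month counting |
|---|---|---|
| 3-month build-up | 0.70 / 0.93 = 0.75 | 0.55 / 0.88 = 0.63 |
| 6-month build-up | 0.38 / 0.82 = 0.46 | 0.27 / 0.77 = 0.35 |
| 12-month build-up | 0.07 / 0.61 = 0.11 | 0.02 / 0.58 = 0.03 |

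A fade to zero over 12 months gives 1.03 / 0.46 = 2.24 (about 2.0 to 2.3 depending on which waves are pairs). A fade to half gives 1.39-1.45. With a linear trend instead of month effects, month-end counting gives 0.78, 0.48 and 0.02-0.03 for the three build-ups and 2.38-2.40 for the 12-month fade.

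**5. The same step with no calendar-time term,** as in the DHI model: ratios of 0.95 to 1.08 across these curves and a faster fade to zero over 6 months.

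**The case against.** **The criticised model is not written down.** The 0/1 term appears only for the DHI, in a model without calendar time. The secular trends appear only for DHT/CRM, in a sentence that gives no coding. A reader might infer that the plan fixes a trend-adjusted single step for every ED-level outcome, the DHI included. The documents do not support that. The DHI model as written shows an error within about 8%, and the sentence on secondary outcomes does not say that secular trends are carried over. The full DHT/CRM specification may sit in the analysis plan, which is not shown. This stands and makes the point conditional. What remains is that the launch-date rule, the pre/post framing and Table 1 all point to one immediate step.

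**The size depends on assumed curves.** A reader might take a two- to threefold error as a property of the layout. It is not. No uptake or decay curve is given, and the ratio runs from mild to extreme across plausible ones. Moving an assumed 6-month ramp by half a month shifts it from 0.46 to about 0.35. This also stands.

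**Uptake is measured and modelled.** Provider use of the CME, website, app and reminders is to enter the DHT/CRM model, and CME use is to be explored. These variables could absorb some slow uptake. But they are provider behaviour after launch: conditioning on them changes what is estimated and loses the randomised contrast. They do not replace an effect of time since launch.

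**Conclusion.** The point holds for the trend-adjusted DHT/CRM analysis, conditional on a single-step coding that the article implies but does not state. In that case the coefficient describes the first few months after launch. It is about 0.6-0.75 of the true post-launch average for a 3-month build-up, 0.35-0.47 for 6 months, near zero to 0.1 for 12 months, and about 2.2 times it for a complete fade over 12 months. If the effect is immediate and constant, there is no bias. The figures assume monthly waves, equal ED sizes and a linear scale.

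The point does not extend to the DHI model as written, and it reaches imaging, admission, length of stay and safety outcomes only where secular trends are adjusted for. It calls for a cheap improvement to the analysis and shows no error in the design.

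**What to change.** State how ED exposure is coded in the DHT/CRM model. Keep the randomised launch date as the start of exposure, and prespecify a second model in which the single term is replaced by categories of time since launch (monthly or two-monthly). Report the effect curve and its average over the months that every ED reaches: about 7 or 8, since the last wave is month 17 of 23 (6 + 11 + 6) or 24. Report this beside the single-step estimate. If the two differ materially, do not read the single-step coefficient as the average programme effect. Do the same for other ED-level outcomes only where secular trends are adjusted for. Fix this before the ED-level results are examined; otherwise label it post hoc.

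The cost is a few more parameters and a standard error about 20-25% larger for that average, at either ICC. Taking Table 1's power of 0.999 as a floor, z = 1.96 + 3.09 = 5.05; dividing by 1.25 gives 4.04, and Phi(4.04 - 1.96) = 0.98 for an effect of the same size. The loss would matter more for effects much smaller than those in Table 1. No new data or design change is needed.

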#### Patient level

##### Initial design

We planned to have 800 patients for analysis of the patient level intervention. We have two concurrent interventions: provider-based intervention (pre-intervention period vs post-intervention period) and patient-based intervention (treatment materials vs standard of care materials). As a result, there will be 4 different groups each with 200 participants: no intervention, provider-based intervention only, patient-based intervention only, both provider- and patient-level interventions. Consistent with 2019 extension of CONSORT guidelines for multi-arm parallel-group trials, [25] our power considerations are based on our two primary comparisons: no intervention vs ED-level intervention,no intervention vs patient-level intervention. To assess power, we consider a clinically meaningful effect size to be a >=15% difference in the DHI outcome between the intervention and control group. In the medical literature, there has been some variation in thresholds of the minimal clinically important change (MIC) for the DHI. In the original derivation of the DHI, an 18-point difference was felt to be the MIC [23]. However, this conclusion was based on standard errors of the difference from test-retest in 14 participants. In a subsequent study of 32 dizziness patients, Tamber et al. found that a change of 11 points (corresponding to a 28% difference) was a strong discriminator of patients who improved by at least 2 points on a global self-report disability measure (the Disability Scale) at 48 h compared with patients who did not improve (c-statistic, 0.83) [51]. Friscia et al. performed a study in 45 dizziness patients and found that an approximately 10% change in the DHI score after 4–6 weeks was strongly associated with the established minimal clinically important difference in the 15-item Global Rating of Change (GROC) scale (c-statistic, 0.80) [14]. In an outpatient clinical trial of an internet-based intervention for vestibular physical therapy and cognitive behavioral coping strategies in patients with chronic dizziness, Geragherty et al. found that the intervention group had a 14% lower DHI compared with the control group [16]. Supporting that the 14% difference is clinically meaningful, 62% of the intervention group reported overall improvement compared with 33% of controls (*p*<0.001) [16]. For DIZZTINCT-2, we concluded that it was best to ensure that we have power to detect the lower range of a minimal clinically important difference between groups (i.e., 15%) for two main reasons: (1) Given that our interventions are low risk, scalable and applicable to a large target population, even a relatively small effect size would likely justify wide implementation and (2) If our intervention also improves the efficiency of care, then even a very small improvement in clinical outcomes would also justify wide implementation.

For our power calculation, we expect the baseline DHI in these acute ED dizziness presentations to be approximately 60 [2, 17, 18, 22, 24, 34, 37, 48, 52]. In the short-term follow-up period, we expect the non-intervention groups to improve by approximately 30% [6, 52], corresponding to a mean outcome DHI of 42. We consider the MIC for the intervention groups compared with the control group to be 15%, corresponding to a mean outcome DHI of 35.7. A more than 15% difference will exceed Jacobson’s original threshold of change in baseline of 18 points for the intervention group,70 and also differ from the control group by the ~10% threshold identified by Friscia et al as an MIC [14]. Based on the medical literature, we expect the standard deviation (SD) of DHI outcomes in our population will be 20–50% of the mean [18, 37, 52]. For our power calculation, we use a SD of 16 which is the high end of the estimate.

To calculate power for the patient-level intervention, we used two-sample means test and adjusted the estimate considering the effective sample size accounting for the ICC of the ED-facility that we found in DIZZTINCT-1 (1.9%). For this comparison, we have a power of 0.97 to detect a 15% difference in DHI outcome (35.7 vs 42) with our target sample size of 200 per group (Table 2). To achieve a power of 0.80, we would only need 113 patients per group. If larger differences in the intervention and control groups are obtained, then our power increases accordingly.

**Table 2 Tab2:** Power calculations for patient-level intervention differences in dizziness handicap inventory outcome in intervention vs control population

Control, mean outcome (DHI*)	Intervention, mean outcome (DHI*)	Outcome difference b/t treated and control	SD	Alpha	ICC**	Power for 400 subjects (200 per group)	Minimum sample size for power >0.8
42	31.5	25% better	16	0.05	1.9%	1.0	96 (48 per group)
42	33.6	20% better	16	0.05	1.9%	0.99	136 (68 per group)
42	35.7	15% better	16	0.05	1.9%	0.97	226 (113 per group)
30	25.5	15% better	12	0.05	1.9%	0.95	246 (123 per group)
20	17	15% better	8	0.05	1.9%	0.95	246 (123 per group)

Shaded row indicates the power calculation for the prespecified threshold of a 15% difference between intervention and control groups. Calculations made using two sample means test accounting for ICC of 1.9%

**DHI* dizziness handicap inventory

***ICC* intraclass correlation coefficient

ICC for Aim 2 power patient-level intervention is at the ED-level since this is where more clustering will occur in Aim 2.

To calculate power for how the ED-level intervention impacts the patients enrolled in the trial (and thus contributing a DHI, in contrast to the larger cohort of patient only contributing data from the electronic health record) (Table 2), our calculations were made by including the number of clusters (12 ED facilities) and cluster heterogeneity using the ICC (1.9%) (Table 3). For this comparison, we have a power of 0.89 to detect a 15% difference in DHI outcome (35.7 vs 42) with our target sample size of 200 per group (Table 3). To achieve power of 0.80, we would only need 132 patients per group.

**Table 3 Tab3:** Power calculations for ED-level intervention differences in dizziness handicap inventory outcome in intervention vs control population

**Control, mean outcome (DHI*)**	**Intervention, mean outcome (DHI*)**	**Outcome difference b/t treated and control**	**SD**	**Alpha**	**ICC**	**Power for 400 subjects (200 per group)**	**Minimum sample size for power >0.8**
42	31.5	25% better	16	0.05	1.9%	1.0	96 (48 per group)
42	33.6	20% better	16	0.05	1.9%	0.99	144 (72 per group)
42	35.7	15% better	16	0.05	1.9%	0.89	264 (132 per group)

Shaded row indicates the power calculation for the prespecified threshold of a 15% difference between intervention and control groups. Calculations made considering stepped wedge design at 15 sites accounting for ICC of 1.9%

**DHI* dizziness handicap inventory. *ICC* intraclass correlation coefficient. ICC for Aim 2 power patient-level intervention is at the ED-level since this is where more clustering will occur in Aim 2

The additional power protects us against unexpected problems with recruiting or retention and also allows for additional exploratory analyses of differences in benefit based on symptom and patient characteristics.

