##### Sample size revised

After initiating a process change allowing patients to self-enroll into the study, recruitment in the patient level intervention accelerated. The trial leadership, in consultation with the independent medical monitor and a representative from the sponsoring institute, elected to increase the maximum sample size for this group, to ensure adequate sampling before and after the provider level intervention in each site. The increased size also allows for increased power in important subgroups (fully specified in the statistical analysis plan). Patients with either BPPV or vestibular neuritis may represent as little as 20% of the overall cohort and we anticipate most of the benefit of the patient level intervention will be in these groups. Finally, we felt that there was a low risk of having excess power. The risk of demonstrating a numeric difference in the DHI that is not clinically relevant was considered low. In addition, the non-response patterns of participants across the 4 weeks of follow up surveys for the DHI introduce another issue that could reduce the effective power of the trial. This operational decision to increase sample size was made by the trial leadership, who did not have access to the outcome data by treatment assignment at the time of the decision. Based on enrollment projections, the maximum allowed sample size was set at 2000 (based on the plan for 6 months of recruitment following the last site level intervention), although the most likely final sample size is around 1500. In addition, the standard deviation of the DHI was higher than expected—therefore power was likely lower than our pre-trial assumptions.

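### The planning SD of 16 for the DHI is not the high end of the plan's own range (50% of 42 is 21), so the stated powers are not those at the top of that range

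*Protocol article*

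**What the plan says.** All of this is in the Protocol article, Sample size {14}, Patient level.

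- **Means (Initial design).** The control group is expected to improve by 30% from a baseline of about 60, "corresponding to a mean outcome DHI of 42". The intervention target is 15% lower, "corresponding to a mean outcome DHI of 35.7".
- **SD range (Initial design).** "we expect the standard deviation (SD) of DHI outcomes in our population will be 20–50% of the mean".
- **SD chosen (Initial design).** "For our power calculation, we use a SD of 16 which is the high end of the estimate".
- **Patient-level result (text and Table 2).** "we have a power of 0.97 to detect a 15% difference in DHI outcome (35.7 vs 42) with our target sample size of 200 per" arm. On the minimum size the article adds: "To achieve a power of 0.80, we would only need 113 patients per group". The ICC is 1.9%.
- **ED-level result (text and Table 3).** With the same means, SD and ICC, the power is 0.89 at 200 per group, and 132 per group are needed for 0.80. The text counts 12 facilities; the table note counts 15 sites.
- **Use made of the result.** The paragraph after Table 3 treats the excess over 80% as a reserve against recruitment and retention problems and as room for exploratory analyses.
- **Later statement (Sample size revised).** The maximum is raised to 2000, with about 1500 thought most likely, and "the standard deviation of the DHI was higher than expected—therefore power was likely lower than our pre-trial assumptions".

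**The concern.** The range and the label sit in adjacent sentences and do not agree. Half of 42 is 21, and half of 35.7 is 17.85; 16 lies below both. A reader told that the SD sits at the high end will take 0.97 and 0.89 as powers that already allow for the largest SD the investigators expected, and will accept the reserve claimed after Table 3. If the SD is nearer the true top of the range, much of that reserve goes for the patient-level comparison. For the ED-level comparison it goes entirely at the initial 200 per group. The article names both as primary comparisons.

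The mislabel also blurs the later admission. An SD between 16 and 21 would be higher than the planning value yet inside the stated range, so the reader cannot tell whether the range failed or only the value picked from it.

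**Working it through.** **Inputs.** Means 42 and 35.7 (difference 6.3), SD 16, alpha 0.05, ICC 1.9%, 200 per group, all from Initial design and Tables 2 and 3. A two-sided test is assumed, because sidedness is not stated for the DHI comparison.

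**1. Where 16 lies in the range**
- Control mean: 0.20 × 42 = 8.4 and 0.50 × 42 = 21; 16/42 = 0.38.
- Intervention mean: 0.50 × 35.7 = 17.85; 16/35.7 = 0.45.
- Other 15% rows of Table 2: 12/30 = 0.40 and 8/20 = 0.40.

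The table is built at about 40% of the control mean, not 50%.

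**2. Reproducing Table 2.** Two-sample t-test, standardised difference d = 6.3/16 = 0.394.
- Unadjusted power at 200 per group is 0.975, and 103 per group are needed for 80%.
- The clustering adjustment is not written out. Adding 10 per group to the unadjusted t-test size gives every row of Table 2: 38, 58, 103, 113 and 113 become 48, 68, 113, 123 and 123.
- Taking 10 off the 200 gives power 0.969 at an effective 190, matching 0.97.

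The stated figures are therefore right for SD 16.

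**3. Table 2 at the top of the range**

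| SD | Power at 200 per group, unadjusted | With the implied allowance | n per group for 80%, unadjusted | With the implied allowance |
|---|---|---|---|---|
| 16 | 0.975 | 0.97 | 103 | 113 |
| 21 (50% of 42 in both groups) | 0.85 | 0.83 | 176 | 186 |
| 19.5 (50% of each group's own mean) | 0.90 | 0.88 | 152 | 162 |

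The 19.5 is √((21² + 17.85²)/2).

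**4. Table 3.** No formula is given. I tried a design effect, DE = 1 + (m − 1) × 0.019, where m is 400 divided by the number of sites.
- 15 sites: m = 26.7, DE = 1.488, effective n = 200/1.488 = 134. At SD 16 the power is 0.896 and 136 per group are needed, close to the stated 0.89 and 132. At SD 21 the power is 0.69 and about 310 per group are needed (m grows with n).
- 12 facilities: m = 33.3, DE = 1.614, effective n = 124. At SD 16 the power is 0.87. At SD 21 it is 0.65, and about 387 per group are needed.

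This is an inferred method. It fits the 15% row approximately but not the 25% row, where it gives 41 per group against the stated 48. The Table 3 results are therefore a range.

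**5. Revised sample.** If 1500 split equally over four groups, each has 375. At SD 21:
- Patient-level comparison, unadjusted: 0.98.
- ED-level comparison, 15 sites: DE = 1 + (50 − 1) × 0.019 = 1.931, effective n = 194, power 0.84.
- ED-level comparison, 12 facilities: DE = 1 + (62.5 − 1) × 0.019 = 2.168, effective n = 173, power 0.79.

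**The case against.** The strongest reply is that the practical consequence is already disclosed. The tables belong to the initial design. The next subsection says the SD was higher than expected, names non-response as a further loss of power, and enlarges the sample. Enrolment closed in March 2025, so no recruitment decision now turns on Table 2. This stands, and it limits how much the point matters. It does not remove the error: the label and both tables remain, and the admission carries no SD and no power.

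Second, the range does not say which mean it refers to, and using 21 in both groups is the harshest reading. That is fair. Half of each group's own mean gives 0.90 and 152 per group, unadjusted. Under that reading 16 is still below the top of the range.

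Third, the planned analysis is a multi-level model with baseline severity and up to four assessments per patient, which would usually be more precise than a raw two-sample test. This also stands. The gain cannot be put in numbers because no correlations are given, so the figures here describe the article's own calculation, not the final model.

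A reader might infer three stronger things that the text does not support:
- That the trial is underpowered. At 200 per group the Table 2 comparison stays above 0.80 at SD 21, and about 1500 participants largely restore both comparisons.
- That the powers were offered as worst-case. The article applies its label to the SD, not to the power.
- That the team holds a blinded pooled SD. The article says only that the SD was higher than expected and that trial leadership had no outcome data by assignment when it enlarged the sample.

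**Conclusion.** The statement about the SD is wrong on the article's own figures. Sixteen is 38% of the control mean and 45% of the intervention mean, while the stated upper end is 50%. The 0.97 and 113 are correct for SD 16 but are not the figures at the top of the range.

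At the initial 200 per group, the patient-level comparison loses about 12 to 14 points of power at SD 21, or about 7 to 9 points if 50% is applied to each group's own mean, and stays above 0.80. The ED-level comparison falls below 0.80 under each design effect tried, subject to the uncertainty about Table 3's method. At about 1500 participants only the ED-level comparison with 12 facilities sits marginally under 0.80.

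These results assume a two-sided 5% test, equal groups, a single outcome per patient and complete follow-up. The error deserves correction because the justification draws a reserve of power from it. It is a misstatement in the sample-size text, not evidence that the enlarged trial cannot answer its questions.

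**What to change.** 1. Describe the SD of 16 as about 40% of the control mean, and remove the statement that it is the high end.
2. Add rows at SD 21 to Tables 2 and 3. State the clustering formula and the number of sites used, and settle whether Table 3 rests on 12 or 15.
3. In Sample size revised, give the SD that is called higher than expected, computed without regard to treatment assignment. State power at about 1500 and at 2000 for that SD and for SD 21, separately for the two primary comparisons.
4. Reword the sentence after Table 3 on additional power so that it matches the restated figures.

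The cost is a text and table correction. No patients are added; the only downside is that the stated power becomes less favourable.
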